### 2.3. Study Visits

Patients are scheduled to five visits at the clinic during the study. Telephone consultations are made during the titration phase, at follow-up, and by need. The electronic diary (e-diary managed by REDCap^®^) is completed during baseline and during the study treatment phase. Echocardiogram, biochemistry, medical examination, clinical tests, and so forth are performed during the study, as illustrated in Table 2.

### 2.4. Randomization and Blinding

Randomization is performed centrally at Glostrup Pharmacy using a computer-generated randomization list. Patients are randomized to the project after baseline if they are eligible. Block randomization is used at three sites (AUH, DMSC, and SCIWDK) and for the sub-study to ensure an approximately equal number in each treatment arm. No stratification is performed. The study is double-blind (patients, health care providers, and investigators/outcome adjudicators). Randomization codes are stored at the pharmacy until the project is completed. Randomization for the individual patient will only be broken in the case of serious adverse events (SAE), serious adverse reactions (SAR), or suspected unexpected serious adverse reactions (SUSAR). If the code is broken for an individual patient due to SAE, SAR, or SUSAR, only the study sponsor will know to which treatment arm they belong. Hence, treatment will still be blinded for investigators and statisticians. 

### 2.5. Intervention

The project medicine contains cannabinoids/placebo and is manufactured and packaged at Glostrup Pharmacy. Both the placebo and the three active treatments are given as an oral treatment in capsules.

One capsule contains: Hard gelatin capsule, white size 1 (HGC SIZE 1, Capsule). The empty capsules consisted of 2% titanium dioxide (Ph, Eur), qsq. 100% Gelatin (Ph.Eur) Excipients: Ascorbyl palmitate Ph.Eur. 0.2 mg, Hard Fat Ph.EUR Ad 0.5 mL, as well as an active component in the form of either:(1)Dronabinol (THC): Dronabinol natural DAC 2.5 mg (maximum daily dose 22.5 mg); or(2)Cannabidiol (CBD): Cannabidiol, synthetic DAC 5 mg or (maximum daily dose 45 mg); or(3)Dronabinol (THC) + Cannabidiol (CBD): Dronabinol natural DAC 2.5 mg and Cannabidiol, synthetic DAC 5 mg (maximum daily dose 22.5 mg THC and 45 mg CBD); or(4)Placebo: No active components.

The capsules are identical without smell, taste, color, or other characteristics that could lead to unblinding.

The selected maximum doses of the project medicine have been chosen to ensure that all patients reach an adequate dose to cover symptoms. The slow up-titration ensures that the best-tolerated dose is reached for each patient [52].

### 2.6. Outcome Measures 

Primary endpoint evaluation (main study):(1)Pain intensity (PI): Average pain score in the diary during the past 7 days of active treatment at a stable dose (week 6) compared with the 7-day baseline period (NRS 0–10, where 0 is no pain and 10 is the worst possible pain).(2)Degree of spasticity: Average spasticity score in the diary during the past 7 days of active treatment at a stable dose (week 6) compared with the 7-day baseline period (NRS 0–10, where 0 is no spasticity and 10 is the worst possible spasticity).

We hypothesized that there is no difference (0-hypothesis) between active treatment and the placebo when it comes to the primary endpoints (NP and spasticity) or adverse reactions. 

Secondary endpoint evaluation (main study):(1)Patient Global Impression of Change (PGIC, 7-point scale from greatly worsened to greatly improved)(2)Quality of Life (EQ-5D) [53]

Other endpoints

(1)Number of responders with 50% pain reduction/50% reduction of spasticity (diary)(2)Pain relief and relief of spasticity (complete, good, moderate, mild, no, worsening, diary)(3)The effect on various pain symptoms (NPSI) [54](4)Use of escape medicine (paracetamol, diary)(5)Spasticity assessed on the Modified Ashworth Scale [55](6)The influence of pain and spasticity on activities, mood, and sleep (NRS 0–10, diary)(7)Sleep (rated with NRS; 0: No sleep problems; 10: Worst possible sleep problems, diary)(8)Sleep (PROMIS, diary) [56](9)Stress (PASAT, questionnaire) [57](10)Cognition (SDMT, Symbol Digit Modalities Test) [58](11)Coordination (MS), 9-hole peg test [59](12)Anxiety and depression (PROMIS, diary) [60](13)Patient’s expectation of pain relief (diary) (predictor)(14)Trail Making Test A and B [61](15)Blinding (the patient must indicate what he/she thinks he/she has received at week 3 and 6)(16)Side-effects (e-diary and visits) (list; dry mouth, headache, depression, nightmare, euphoria, dizziness, tinnitus, anxiety, hallucinations, fatigue/drowsiness, palpitations, flushing of the face, stomach ache, nausea, diarrhea, muscle pain, visual disturbances, and other (open question)).

Sub-study: (1)PK and PD (maximum plasma concentration (Cmax), minimum plasma concentration (Cmin), average plasma concentration (Cavg), mean steady-state area under the curve (AUC_0-24_), Tmax, Tmin).(2)The pharmacodynamic parameters: Pain intensity (PI), pain intensity difference (PID), pain relief, patient and investigator global evaluation.(3)Pain registration on a NRS 0–10(4)At the same time as the pain assessment, general questions are answered on a NRS of 0–10.

### 2.8. Sample Size

For the main study, we calculated a standard deviation of 3.5 (SD3.5), an effect of 1 point on the NRS scale (difference from baseline mean NRS 5 to mean NRS 4 in treatment week 6), and a power of 80%. Considering four treatment arms and an uneven distribution in pain and spasticity, we expect that only about 40% of pwMS suffer from both pain and spasticity (opposite to about 70% in pwSCI). We aim to include 112 patients in each treatment arm (*n* = 448) (*n* = 480 when adjusting for drop-outs).

For the sub-study, the expected kinetics/dynamics are unknown. This is an exploratory study and no power calculation has been made.

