## 2. Materials and Methods

### 2.1. Study Design and Settings

The study is designed as a national multicenter randomized double-blind, placebo-controlled parallel study (RCT). Patients are randomized to one of four treatment arms: THC, CBD, THC and CBD, or placebo.

The study is coordinated by the steering committee with representatives from the Dept. of Neurology, Aarhus University Hospital (AUH); the Spinal Cord Injury Centre of Western Denmark (SCIWDK); the Danish Pain Research Center; the Dept. of Clinical Medicine, Aarhus University; the Danish Multiple Sclerosis Centre; the Dept. of Neurology, Copenhagen University Hospital-Rigshospitalet (DMSC); and the Dept. of Clinical Pharmacology, AUH. The Danish MS clinics and the two national SCI clinics participate in the study. The study plans to include 448 patients for the main study and 40 patients for the sub-study. All patients are randomized to one of four treatment arms (Figure 1). THC is naturally extracted from the *cannabis sativa* plant. CBD is synthetically produced. Maximum daily doses are THC = 22.5 mg and CBD = 45 mg. 

The treatment duration is 7 weeks in total, with endpoints evaluated at the end of the sixth week. Previous studies suggested an effect after 4–5 weeks of treatment [34,49] Standard Protocol Items: The Consolidated Standards of Reporting Trials (CONSORT) 2010 checklist and flow diagram will be used when presenting the results of the present study.

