## Figures and Tables

**Figure 1 brainsci-11-01212-f001:**
[figure not shown]
Flow diagram.

**Table 1 brainsci-11-01212-t001:** Inclusion and exclusion criteria.

	Inclusion Criteria
1	Definite or probable NP [1] for more than 3 months with mean pain intensity in baseline NRS > 3 and NRS ≤ 9 and/or presence of spasticity of more than 3 months with an intensity of >3 (NRS)
2	Stable disease (for pwMS; no relapse within the past month and no change in disease-modifying treatment during the previous three months).
3	Age ≥ 18 years
4	Informed consent is available.

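### The stated 80% power rests on a before-after change within an arm; on the same inputs no between-arm test that the plan describes reaches it (about 57% for active versus placebo at 112 per arm).

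*Protocol article*

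**What the plan says.** Section 2.8 (Sample Size) gives these planning inputs: "we calculated a standard deviation of 3.5 (SD3.5"), 80% power, and "an effect of 1 point on the NRS scale (difference from baseline mean NRS 5 to mean NRS 4 in treatment week 6"). It states no placebo response, no between-arm difference, no alpha and no sidedness. It then mentions the four arms and an uneven distribution of the two symptoms, and says "we expect that only about 40% of pwMS suffer from both pain and spasticity", against about 70% of patients with spinal cord injury (SCI). The result is "We aim to include 112 patients in each treatment arm", 448 in total, or 480 after allowing for drop-out.

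Section 2.6 (Outcome Measures) sets the hypothesis between arms: "We hypothesized that there is no difference (0-hypothesis) between active treatment and the placebo when it comes to the primary endpoints". Section 2.7 (Statistics) analyses differences between treatment arms by one-way analysis of variance or Kruskal-Wallis. It counts a patient who has only one of the two symptoms at inclusion for that endpoint alone.

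Table 1 limits entry for pain to "mean pain intensity in baseline NRS > 3 and NRS ≤ 9". For spasticity the intensity must exceed 3, with no upper limit below the end of the scale.

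**The concern.** The effect in the sample size statement and the effect tested are different quantities. A fall from 5 to 4 within a treated arm says nothing about how far that arm differs from placebo. A comparison of two arms also carries the sampling error of both, so on the same SD it needs about twice as many patients per arm as a before-after test. In addition, 112 is a count of all patients in an arm, while each primary endpoint uses only those with the symptom.

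Section 4 lists the relatively large sample as a strength, and section 2.10 commits to publishing a negative result. If power against the planned difference is well below 80%, a null result could be taken as evidence against the cannabinoids when the trial had a substantial chance of missing the effect it was planned to find.

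**Working it through.** **Inputs.** Difference d = 1, SD = 3.5, 112 per arm, four equal arms, 40% of MS and 70% of SCI patients with both symptoms (all from 2.8, except equal arms from 2.4). Alpha is not in the document; two-sided 5% is assumed, with one-sided 5% shown as a range. The SD of 3.5 is taken as that of the analysed quantity, also an assumption. Power figures use the t distribution unless noted.

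**1. Trying to reproduce 112.** With z(0.975) + z(0.80) = 2.80:
- Before-after within one arm: n = SD² × 2.80² / d² = 12.25 × 7.85 = 96, or about 98 with the t distribution. At 112 this test has 85% power.
- Two arms: n = 2 × 12.25 × 7.85 = 192 to 193 per arm.
- Two arms, one-sided 5%: 152 per arm (normal approximation).
- Four-arm ANOVA with all three active arms 1 point better: 180 per arm. With two arms against two: 135.
- Three active arms pooled against placebo: 129 in the placebo arm (normal approximation).

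None of these gives 112. The before-after figure falls below it and every between-arm figure lies above it.

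**2. Power of between-arm tests at the planned size.** For two arms the noncentrality is d / (SD × √(2/n)). At n = 112 it is 1 / (3.5 × √(2/112)) = 2.14.

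| Test | Power |
|---|---|
| Active versus placebo, 112 per arm, two-sided 5% | 57% |
| Same, one-sided 5% | 69% |
| Same, two-sided, all 480 analysed (120 per arm) | 60% |
| Four-arm ANOVA, all actives 1 point better | 58% |
| Four-arm ANOVA, two arms against two | 71% |
| Pooled actives versus placebo (336 versus 112) | 74% |

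**3. Patients evaluable per endpoint.** If every patient has at least one symptom and a share p has both, the two endpoints together count 1 + p per patient, so the average share per endpoint is (1 + p)/2.
- MS: (1 + 0.40)/2 = 70%, and 0.70 × 112 ≈ 78 per arm.
- SCI: (1 + 0.70)/2 = 85%, and 0.85 × 112 ≈ 95 per arm.

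Active-versus-placebo power is 43% at 78 and 50% at 95. Section 2.2 expects more MS than SCI patients, which points to the lower end. With an uneven split of single-symptom patients, one endpoint gains what the other loses, so at least one falls below its average. In the extreme, with 40% evaluable in MS (about 45 per arm), power is 27%.

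**4. What 3.5 can be.** On a range from a to b with mean m, the largest possible SD is √((m − a)(b − m)). At a baseline mean of 5:
- Pain, above 3 and up to 9: √(2 × 4) = 2.83.
- Spasticity, above 3 and up to 10: √(2 × 5) = 3.16.

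So 3.5 cannot be the baseline SD of eligible patients. Eligibility does not exclude it as the SD of a week-6 score or of a change.

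**5. What would give 80%.**

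| Evaluable per arm | Detectable difference at SD 3.5 | Largest SD for a 1-point difference |
|---|---|---|
| 112 | 1.32 | 2.66 |
| 95 | 1.43 | 2.45 |
| 78 | 1.58 | 2.22 |

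**The case against.** The strongest reply concerns the SD. Section 2.8 does not say what 3.5 measures, and if the analysed quantity varies less, power is better. At an illustrative SD of 2.5, power would be 85% at 112 per arm and 70% to 78% at 78 to 95; at 2.0 it would be 87% to 96% over the whole range. A reader might infer from the 57% that the trial is certainly underpowered. The document does not support that. It shows only that the claim fails on the inputs given to justify it.

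Alpha is also absent and may stand in the full protocol, so 57% is not purely the plan's own figure. This stands as a caveat, but one-sided 5% still gives only 69%.

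A reader might infer that 112 came from a paired calculation. That is not shown: the paired formula gives about 98, and 112 may already contain an allowance for the four arms and the symptom mix. Nor does the 80% hold cleanly for a before-after test, since at 78 to 95 evaluable patients that test has 70% to 79% power.

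Withdrawn patients stay in by last observation carried forward, so up to 120 per arm could be analysed. With 70% to 85% evaluable (84 to 102 per arm), power would be 45% to 53%, a little above the 43% to 50% range. A factorial main effect, 224 against 224, would reach 85%, but the article describes no such analysis, and on evaluable patients it falls to 71% to 79%.

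Finally, 448 and 480 might look contradictory. Section 2.8 explains the second as the drop-out adjustment, and 2.2.2 places the 40 sub-study patients within the main study, so no conflict arises there.

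**Conclusion.** The point holds as a mismatch between the stated power and the tests planned. Section 2.8 describes a within-arm change, and on its difference, SD and arm size no between-arm test that the plan describes reaches 80%. Under two-sided 5% and an analysis SD of 3.5, power for active versus placebo is about 57% at 112 per arm, against a requirement of about 193.

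The 43% to 50% range per endpoint is more conditional. It also needs the 40% and 70% to describe enrolled patients, every patient to have at least one symptom, and single-symptom patients to split evenly. How 112 was derived is unknown, and the trial's actual power cannot be known until the SD is defined and justified.

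**What to change.** Restate section 2.8 for the between-arm test that will be run, separately for pain and spasticity. For each endpoint give the expected evaluable number per arm, the alpha and sidedness, the between-arm difference, and an SD with its source and the quantity it describes. The blinded pooled SD from data already collected would serve, since unblinding follows the last patient's last visit (2.9). Replace the 80% by the resulting power and the detectable difference, which at SD 3.5 is about 1.3 to 1.6 points.

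The cost is one rewritten section and one blinded calculation. No extra patients are needed and nothing in the conduct of the trial changes. The drawback is that the stated power will probably be less favourable.

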### 2.9. Ethical Considerations and Safety

The study complies with the law on the processing of personal data. Trial participants receive both written and oral information before inclusion in the study and the voluntary nature of their participation will be emphasized. The patient may withdraw their informed consent for the project without justification at any time. Data from the project are stored electronically in REDCap^®^ (Aarhus University, Aarhus, Denmark), which can only be accessed by the project participants and monitors. REDCap^®^ is a secure web platform for building and managing online databases and surveys. Unexpected AEs are not expected, as the dose of THC and CBD in this study is at the same level or lower than in comparable studies [50]. In the study, patient safety is highly valued. Patients receive standardized treatment with a slow up-titration, and individual adjustment can be performed. Patients are associated with a single clinic, where they come for scheduled check-ups. All patients receive a personal contact card. All side-effects and AEs are documented. If an AEs are tolerable or unrelated to the study medication, treatment can continue with a close collaboration between the investigator/sponsor and the patient. If an AE is intolerable, patients are able to withdraw from treatment. SAE, SAR, and SUSAR are reported to the health authority within the timeframe set by Danish law, and a yearly safety report will be performed. Driving motorized vehicles is not permitted when on study medication. All women between menarche and post-menopause are defined as fertile, unless permanently sterile. Anticonception (as defined by the Danish Ministry of Health) should be used during and 3 months after treatment. Pregnancy tests will be performed for fertile women before enrollment and during the study.

Un-blinding will be performed after the last patient’s last visit (LPLV). If desired (stated at inclusion), study participants will receive a layman summary.

### 2.10. Publication

The results of the trial will be published in a recognized international journal regardless of the outcome (positive, negative, or inconclusive). The Vancouver recommendations for authorship will be followed. The results of the sub-study may be published independently.

## 3. Trial Status

The inclusion of patients was initiated in February 2019 and will continue until December 2021 at the latest.

## 4. Discussion

Previous studies have shown diverse results when it comes to CBM for treating NP and spasticity in pwMS and pwSCI. Recent reviews and recommendations all recommend more studies and evidence, as studies of the efficacy of CBD are especially lacking. The demand for CBM from patients and society is increasing, and treatment strategies are much sought-after.

The main aim of the present study is to investigate the effects and side-effects of CBM in pwMS and pwSCI. The study has numerous strengths. First, it is an investigator-initiated trial. Second, we use a relatively large sample size to reduce potential bias. We decided to investigate two patient groups with similar symptoms. It is plausible that their nerve damage is comparable, even though MS and SCI have different etiologies. Despite such potential differences in etiology, treatment of symptoms following nerve damage could be consistent [62,63]. Hence, we seize the opportunity to combine two patient groups in this study. Third, we have thoroughly conceived the study design. We investigate the two most widespread cannabinoids (THC and CBD) alone and in combination in a formulation where we know the exact amount of the administered drugs. By using capsule formulation, we limit the risk of unblinding. Fourth, we warrant an adequate dose of CBM in a secure setting with the possibility of individual adjustment. To avoid the need for imputation for the primary outcome, we ask all patients to continue to fill in their diaries even if they drop out of the study. Fifth, we have a proper setting for the PD/PK sub-study, investigating the metabolism of cannabinoids in a patient population. Finally, we make an extensive examination of side-effects.

The present study also has some limitations. It can be difficult to reach the desired number of participants. We have a strict set of exclusion criteria. Participants are not allowed to drive during the study, which can cause lower levels of engagement and a shift toward older and more advanced participants (as they may be less dependent on driving). The maximum dose of THC is in accordance with the doses in Sativex and dronabinol, and has been chosen to minimize the risk of side-effects. The maximum dose of CBD has been chosen to increase the possibility of effect. However, as no prior dose-response study has been performed, we may be at risk of either over- or under-dosing in this study. The availability of cannabinoids, especially CBD, has increased exponentially in recent years, and many patients already use CBD. Patients who experience an effect of CBD/CBM on their symptoms may be less willing to participate in the study, which can lead to underreporting of effects. The duration of treatment is limited to 7 weeks with a follow-up after 1 month. Therefore, we will not able to address the long-term effects or side-effects. The possibility of extension was discussed, but extension would lead to other issues (e.g., maintaining the blinding). There is a risk of unblinding due to the side-effects of CBM, but we will assess blinding success by asking the patients what treatment they think they have received.

The effect parameters in this study are primarily patient-reported outcome measurements (PROMS), which have been chosen to evaluate the patient’s perspective on the impact of treatment on their symptoms. However, the PROMS may have limitations because it is an individual and subjective outcome. We minimize the risk of recall bias by using a continuous daily diary during the study. To ensure a proper registration of side-effects, patients are asked predefined symptoms in a questionnaire, and they have the choice to report additional side-effects.

## Figures and Tables

**Figure 1 brainsci-11-01212-f001:**
[figure not shown]
Flow diagram.

**Table 1 brainsci-11-01212-t001:** Inclusion and exclusion criteria.

	Inclusion Criteria
1	Definite or probable NP [1] for more than 3 months with mean pain intensity in baseline NRS > 3 and NRS ≤ 9 and/or presence of spasticity of more than 3 months with an intensity of >3 (NRS)
2	Stable disease (for pwMS; no relapse within the past month and no change in disease-modifying treatment during the previous three months).
3	Age ≥ 18 years
4	Informed consent is available.
	**Exclusion Criteria**
1	Competitive pain diseases (such as diabetic neuropathy) that cannot be distinguished from the patient’s pain due to SCI or MS
2	Opioid treatment that cannot be discontinued
3	Previous psychiatric disease in patient or nearest biological family, except well-treated depression
4	Previous risk of suicide assessed by the Columbia Suicide Severity Rating Scale [50]
5	Pregnancy and breast-feeding
6	Liver or renal insufficiency
7	Cardiovascular disease (except well-treated hypertension)
8	Previous convulsions/epilepsy
9	Active cancer disease
10	Previous or current addiction to alcohol/medication/drugs or positive urine screening
11	Current recreational cannabis use, or use within three months
12	Medical cannabis prescribed within 3 months
13	Allergy to cannabis products
14	Scheduled surgery during the study
15	Planned travels abroad during the study

**Table 2 brainsci-11-01212-t002:** Standard Protocol Items.

	Inclusion	Baseline	Randomization	Titration			Stable Phase (Maximum Dose)				Phase Out		Follow-Up
Week	−4–0	0	Week 1 Day 1	1	2	3	4	5	6		7		11
VISIT	1		2			3			4		5		
Medical Examination	x		x							x			
Medical history	x												
Neurological exam.	x									x			
EDSS/ISNCSCI	x												
Heart and lung stethoscopy	x												
MAS	x									x			
Clinical tests													
9-hole peg test			x							x			
PASAT			x							x			
NPSI			x							x			
SDMT			x							x			
Trail making test			x							x			
EQ5D5L			x							x			
PGIC										x			
Others			x			x				x			
Pregnancy test			x			x							
Biochemistry *	x					x				x			
U-stix (Drug/THC)			x										
Electrocardiogram	x					x				x			
Blood pressure	x		x			x				x			
Expectation of relief			x										
Blinding **						x				x			
Dispensing of medicine			x			x							
Returning packaging						x				x		x	
Counting of capsules						x				x		x	
Admission ***									x				
Telephone				x	x	x							x
eDiary		x		x	x	x	x	x	x		x		
Pain (NRS)		x		x	x	x	x	x	x				
Spasticity (NRS)		x		x	x	x	x	x	x				
Relief pain (NRS)						x			x				
Relief spasticity NRS						x			x				
Sleep (NRS)		x		x	x	x	x	x	x				
PROMIS sleep		x				x			x				
PROMIS anxiety/depression		x				x			x				
Influence of pain/spasticity (NRS) -activity, mood and sleep		x				x			x				
Escape medicine				x	x	x	x	x	x		x		x
Side effects/AE				x	x	x	x	x	x		x		x

Legend Table 2: EDSS- Expanded disability status scale, ISNCSCI- International Standards for Neurological Classification of Spinal Cord Injury, MAS -Modified Ashworth Spasticity, PASAST- Paced Auditory Serial Addition Test, NPSI-Neuropathic Pain Symptom Inventory, SDMT-Symbol Digit Modalities test, 5Q5D5L Questionnaire 2009 EuroQol Group EQ-5D™(Danish), PGIC-Patient Global Impression of Change, NRS- Numeric rating scale. AE–Adverse events. * The biochemistry covers sodium, potassium, creatinine, eGFR, ALAT, urea, alkaline phosphatase, bilirubin, total cholesterol, low-density lipoprotein, high density lipoprotein, triglyceride, leukocytes, hemoglobin. INR if in anticoagulation therapy ** Patients are asked what kind of treatment they think they are having (and why). *** The admission for Sub-study II is in the stable phase (preferable in week 6, but 4 and 5 is accepted).
